  - a) Egg reduction rate at 21 days after treatment for the PZQ 60mg/Kg and PZQ 40mg/Kg groups.
  - b) Comparison of frequency and severity of adverse events during the 4 hours after treatment, 24 hours and 21 days, for the PZQ 60mg/Kg and PZQ 40mg/Kg groups.
  - c) Comparison of the variation of hemoglobin (Hb) level at 21 days, 6 months and 12 months after treatment (as related to the baseline measurement), for the PZQ 60mg/Kg and PZQ 40mg/Kg groups.
  - d) Comparison of the variation of weight at 6 months and 12 months after treatment (as related to the baseline measurement), for the PZQ 60mg/Kg and PZQ 40mg/Kg groups.

The flow-chart below illustrates the study design:

[figure not shown]

Rapport with government and community leaders at district, ward, village and school levels will be established in the study area. Informed Consent will be obtained for each participant. For children considered minors written Informed Consent will be obtained from their guardians. Schoolchildren meeting the screening criteria will be recruited continuously, subjects will be examined quantitatively for *S mansoni* ova and semi-quantitatively for *S haematobium*. Two stool samples (2 Kato Katz slides will be prepared from each sample) and one urine sample will be collected within 5 days. Those who fulfill the inclusion and exclusion criteria for enrolment in the trial will be randomized to receive treatment with PZQ within 7 days (+/-1 day).

See Appendix 1 for the schedule of activities. It is estimated that 800 school children will be examined during the baseline study within one month. It is expected that about 240 children (30%) will fulfill the criteria for enrollment in the trial. Participants with positive *Schistosoma spp.* diagnosis who do not fulfill the inclusion and exclusion criteria will be treated with the standard treatment of a single dose of PZQ 40mg/Kg.

Schoolchildren in the treatment groups will be followed up for a total of 12 months post-treatment.

The following baseline screening and follow up visits will be done. As shown in Appendix 1 the baseline study is scheduled to last 23 days. Since enrollment is done continuously, activities of D0 will start on the 8th day after screening and activities of D1 on the 9th day and run concurrently with the screening.

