#### 4.1. Inclusion criteria

- Age 10-19 years
- Infected subjects with an egg excretion of  $\geq 100$  eggs per gram of faeces for *S. mansoni*.
- Those able and willing to be followed up
- Who have given written informed consent for stool, urine and blood samples. In case of adolescents (< 18 years), written informed consent from their parents and their verbal assent to be obtained.

Those who have satisfied the inclusion criteria will be further tested for the following exclusion criteria:

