#### 6.2.2. Stool:

At baseline and during follow-up visits each child in schools within 5 km of the Lake Victoria shore recruited in the study will provide a stool specimen on two separate days at maximum interval of 5 days. Duplicate Kato Katz slides (2 slides) (Katz et al., 1972) will be prepared in the field (using the 41.7mg faecal template) from each stool sample. The prepared Kato slides in the field will undergo quantitative microscopic examination for *S mansoni* ova.

Classification as egg count  $\geq 100$  eggs per gram of faeces for *S mansoni* will be obtained by the mean egg count for the 4 slides collected at baseline.

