### **7. ASSESSMENT OF EFFICACY:**

7.1. Parameter to be measured – egg count, as measured by the Kato-Katz method described above, at baseline, D21, 6M and 12M

The measurement of egg count for each time point will be estimated as the mean of the 4 slides collected (2 slides per sample, 2 samples within 5 days).

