#### 7.2. Methods for assessing efficacy:

- Cure rate will be estimated as the proportion of subjects with negative result at 21 days after treatment.
- Egg reduction rate at 21 days after treatment will be estimated through the following formula:  
 $[1 - (\text{epg2} / \text{epg1}) \times 100]$  where epg1 and epg2 are the geometric mean of  $\log_{10}$  transformed (x+1) numbers of eggs per gram of faeces at the screening survey and the 21st day post-treatment survey.

The same calculations of cure rate and egg reduction rate will be estimated for the 6M and 12M follow-up in order to estimate reinfection rates.

7.3. Analysis: The cure rate and egg reduction rate will be compared between the 2 treatment regimens, PZQ 40mg/Kg and 60mg/Kg.

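### Egg reduction at 6 and 12 months is measured against the same slides that selected the child, so reading it as reinfection understates the return of infection in both arms

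*Protocol*

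**What the plan says.** Protocol section 4.1 admits "Infected subjects with an egg excretion of" at least 100 epg for *S. mansoni*. Section 6.2.2 says that this classification "will be obtained by the mean egg count for the 4 slides collected at baseline". Section 7.1 gives the general rule: "The measurement of egg count for each time point will be estimated as the mean of the 4 slides collected", that is, two slides from each of two stools.

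Section 7.2 defines the egg reduction rate from epg2/epg1, where epg1 is the geometric mean, on log10(x+1), of "numbers of eggs per gram of faeces at the screening survey". No other stool is collected before treatment. The D0 activities in section 3.2 are history, examination, pregnancy test, weight and haemoglobin, and Table 1 lists no further parasitology before day 21.

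Section 7.2 then carries two measures forward to the later visits, the cure rate and the egg reduction rate. Of the latter it says: "egg reduction rate will be estimated for the 6M and 12M follow-up in order to estimate reinfection rates".

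**The concern.** The measurement that selects the child is also the baseline against which the child is later compared. Egg counts vary between slides and between days. A child whose four slides happened to read high is more likely to be enrolled, and one whose slides happened to read low is turned away. At follow-up there is no 100 epg floor, so the group mean falls on re-measurement even if nobody's true egg output has changed.

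At 6 and 12 months the protocol gives this within-arm fall an absolute meaning, namely how much infection has returned. A cohort wholly back at its pre-treatment intensity would show a positive egg reduction rate and could be reported as still partly protected. Both arms carry the same expected error, so comparing them does not reveal it. The mechanism does not depend on treatment failures; it would operate even if every child had been cured at day 21.

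**Working it through.** **Plan's own figure.** The protocol states none for this effect, so there is nothing to reproduce.

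**Inputs from the protocol**
- Entry: mean of four slides at least 100 epg (4.1, 6.2.2).
- Slide: "using the 41.7mg faecal template" (6.2.2), so one egg on a slide is 1/0.0417 = 24 epg.
- The threshold in eggs: 100 × 4 × 0.0417 = about 16.7 eggs over four slides. Poisson error alone gives a coefficient of variation (CV) of 1/√16.7 = 24% at that point.
- Eligible share: "It is expected that about 240 children (30%) will fulfill the criteria for enrollment in the trial" (3.2), that is 240/800.

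**Inputs that are assumptions.** The protocol gives neither the distribution of true intensity nor the within-child variance. Both had to be assumed and varied.

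**Method.** Each simulated child keeps the same true intensity at two surveys of two days × two slides. Children are kept if the first survey averages at least 100 epg. Section 7.2's rate is read as (1 − epg2/epg1) × 100, so the false reduction is

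r = 1 − GM(second survey)/GM(first survey), on x+1.

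The correct answer is zero.

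**Results, intensity calibrated to about 30% eligible** (lognormal with 45-80% infected and SD of log10 0.4-0.7, or gamma with shape 0.2-0.5; 300,000 children per scenario):

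| Day-to-day CV | Extra slide CV | r |
|---|---|---|
| 0 | 0 (Poisson only) | 2-6% |
| 45% | 0 | 6-16% |
| 71% | 0-45% | 12-32% |
| 100% | 58% | 26-50% |
| 100% | 100% | 34-58% |

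One case in numbers: 60% infected, SD of log10 0.5, day CV 71%, no extra slide variation. The geometric means are 260 and 205 epg, so r = 1 − 205/260 = 21%.

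**Results, a middle set of assumptions** (lognormal with geometric mean 60-100 epg and log-SD 1.2-1.4, or gamma with shape 0.35-0.6 and mean 150-250 epg; day log-SD 0.3-0.9; slide overdispersion k 2-5; 400,000 children in each of 12 scenarios): r = 7-39%. With arithmetic means it is 2-12%.

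**What r does to a reported figure.** If true output at follow-up is a fraction f of the pre-treatment level, the reported reduction is approximately 1 − f(1 − r).
- f = 0.5: 1 − 0.5 × 0.93 = 53.5% to 1 − 0.5 × 0.61 = 69.5%. Direct simulation gave about 53-70% for a true 50%.
- f = 0.019, a strong day-21 effect: 1 − 0.019 × 0.93 = 98.2% to 1 − 0.019 × 0.61 = 98.8%. Simulated examples gave 98.3-98.7% for a true 98.1%.

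**Between arms.** With a common GM1, the percentage-point difference is (GM40 − GM60)/GM1, so it is multiplied by about 1 − r (0.93 to 0.61 here). The ratio GM60/GM40 does not contain GM1.

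**Proportion egg-positive.** In the calibrated runs, 5-48% of enrolled children fell below 100 epg on re-survey with no true change, but at most about 2% became negative on all four slides.

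**The case against.** The strongest reply is that nothing the trial formally tests depends on this reading. The primary endpoint is cure at day 21, and the only listed egg-reduction endpoint is also at day 21 (section 3.2). Egg reduction at 6 and 12 months appears in the visit schedule and section 7.2, not in the endpoint list. Section 7.2 draws reinfection from the cure rate as well, and a cohort fully back at pre-treatment intensity would show almost no egg-negative children, so a careful reader would not be misled. Section 10.1 already plans a t test on geometric mean egg output between arms; on the log scale, that is the protected ratio.

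All of this stands, and it limits the weight of the point. It does not remove it. Section 7.2 still assigns the egg reduction rate a within-arm meaning that it cannot bear, and randomisation does not help a within-arm reading.

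The objection to any single figure also stands. A reader might take 7-39% as the error this trial will show. The protocol supplies no variances, and other tenable assumptions give anything from about 2% to 58%.

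A reader might also infer that a cleaner baseline repairs the within-arm estimate: take the second screening stool in children whose first stool alone averages at least 200 epg, since (200 + 0)/2 = 100 makes them eligible whatever the second shows. If the two screening days vary independently, the false reduction does vanish (between −2.5% and +1.0% in simulation). But the stools are at most five days apart (6.2.2), and Appendix 1 schedules the slides on successive working days, whereas follow-up is months later. If both screening days share a fluctuation with an assumed log-SD of 0.3, 0.5 or 0.7, a false reduction of about 8-11%, 16-26% or 33-43% remains. The documents cannot settle which applies.

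**Conclusion.** The point holds for one use of one measure: the within-arm egg reduction rate at 6 and 12 months, read as reinfection. The direction is certain given any within-child variation, because the protocol fixes the same four slides as both entry test and baseline. The size is not known. Everything beyond the 2-6% from counting error rests on assumed day-to-day and slide variation, and even that range rests on assumed intensity distributions.

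A reader might infer that the efficacy comparison is biased. The documents do not support that. Selection precedes 1:1 randomisation, the day-21 cure rate does not use epg1, day-21 egg reduction moves by less than one percentage point in the examples above, and the between-arm ratio is unaffected. A percentage-point difference in egg reduction is shrunk towards zero but keeps its sign. This is worth correcting, but it does not threaten the trial's main conclusion.

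**What to change.** In section 7.2:

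1. Report 6- and 12-month egg output as the 60 v 40 mg/kg ratio of geometric means, in line with the comparison in section 10.1.
2. Describe reinfection by the proportion egg-positive at 6 and 12 months.
3. State that egg reduction against the screening baseline overstates sustained reduction, because the screening slides also selected the child, and that it is not a measure of reinfection.

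If a within-arm figure is still wanted, the second-stool baseline in children whose first stool averages at least 200 epg may be given as a sensitivity analysis only. Its limits should be stated: it assumes that the two screening days vary independently, covers about 53-67% of enrolled children (the heavier infections), and rests on two slides per time point.

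The cost is a change of analysis wording, using data already planned. Eligibility, visits and the day-21 analysis stay as they are. The loss is that a within-arm reduction at 6 and 12 months is no longer offered as a reinfection estimate; the between-arm ratio does not replace it, since it answers a different question.

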## **8. ASSESSMENT OF SAFETY:**

### **Adverse Events**

#### **8.1. Parameters to be measured:**

Occurrence and severity of Adverse Event at 4 hours, 24hs, and 21 days after treatment.

**8.2. Methods:** All AEs will be characterized for: severity grading, relationship to the treatment and seriousness.

Treatment with PZQ will be done in the morning of D0 and the research team will remain at the treatment centre until 18.00 hr. Children administered with PZQ will be observed for at least 4 hours before leaving the school compound.

All schoolchildren enrolled in the study will be administered with a questionnaire 4 hours after treatment for the following signs and symptoms: abdominal pain, nausea, vomiting, diarrhoea, anorexia, fever, headache, dizziness and allergic reaction. Each symptom will be graded as described in Table 1 of Appendix 3. Other symptoms not listed in Table 1 will be graded for severity according to classification in Table 2 of Appendix 3. Also, causal assessment for the adverse events in relation to the drug will be done as: not related, unlikely, possible, probable, most probable or insufficient data to assess (see definitions in Appendix 4). On the following day (Day 1), that is, 24 hours post-treatment, all schoolchildren who received PZQ on Day 0 will be interviewed using the same questionnaire to determine whether they experienced any adverse events. The questionnaire will be repeated on day 21-post treatment. In addition, on day 21 Hb will be measured by digital hemoglobinometer (hemocue) to determine whether increased dosage of PZQ has adverse effects on haemoglobin level.

All AEs will be evaluated for seriousness according to the definitions described in Appendix 5. Any immediate serious adverse events will be managed using a resuscitation kit comprising of intravenous N/saline, Adrenaline, Hydrocortisone and carefully monitored until the adverse event disappears completely. All AEs will be monitored and followed-up until resolution. An adverse event likely to be related to the administration of the investigation product which persists to the end of the trial or any serious adverse event occurring after the termination of the trial and likely to be related to the product, will be followed up by the study physicians until its complete disappearance. The causality of such a serious adverse event will be investigated and recorded. Within 24 hours of its occurrence the Principal Investigator will report such serious adverse event to the TDR Clinical Monitor and TDR Clinical Coordinator by a SAE alert form. A complete SAE report will be sent within 5 working days to the Clinical Monitor and Clinical Coordinator. During the forwarding of the information the anonymity of the subject will be maintained. All this will be done in compliance to applicable regulatory requirements related to the reporting of unexpected serious adverse drug reactions to the regulatory authority(ties) and the ICB/IRB.

**8.3. Analysis:** The frequency and severity of AEs will be compared between the 2 treatment regimens, PZQ 40mg/Kg and 60mg/Kg.

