#### D0 (means 7 days after baseline study +/-1 day)

Clinical history of each schoolchild fulfilling screening criteria using questionnaire will be taken to see if the subject has acute or chronic severe disease, including hepato-splenic schistosomiasis. In addition, the questionnaire will seek to establish a history of adverse reactions associated with PZQ, a history of treatment with PZQ within 30 days and medication (such as antibiotics) currently being used which may affect the results of the present trial. This will be followed by a thorough physical examination by a physician for physical fitness to participate in the trial. Those showing signs and symptoms of clinical malaria will be referred for treatment and excluded from the study and referred for treatment. Childbearing age female subjects will further be tested for pregnancy using the Quickstick™ One step HCG Pregnancy Test. Those tested positive for pregnancy will be excluded from the study. Each girl will be given individual counseling from the study nurse. Those children with schistosomiasis who will be excluded from the study at this point will be treated with a single oral dose of PZQ at 40mg/kg.

For the children who fulfill all criteria for enrolment, body weight will be determined and a finger-prick blood sample will be collected for Hb measurement. Thereafter they will be treated with PZQ according to weight and dosage regimen assigned in the trial (see randomization and blinding section for treatment assignment). During the 4 hours post-treatment study subjects will be observed for occurrence of adverse events and by the end of this period they will be assessed for adverse events using a questionnaire.

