## **6. CLINICAL AND LABORATORY PROCEDURES**

### 6.1. Clinical examination:

#### 6.1.1. Clinical malaria

Signs and Symptoms of clinical malaria will be determined (by one of the study physicians) on schoolchildren recruited in the study after satisfying inclusion criteria before treatment with PZQ. Those with fever (temperature  $\geq 37^{\circ}\text{C}$ ) and/or showing one or more of the following signs and symptoms, i.e., body malaise, headache, vomiting or diarrhoea will be considered to have clinical malaria will referred for treatment at a nearby clinic and excluded from the study.

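### Five of the nine solicited adverse-event symptoms have no planned graded record before dosing, so pre-existing complaints can be counted as adverse events and pull the 60 v 40 mg/kg comparison towards no difference

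*Protocol*

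**What the plan says.** Section 8.2 lists nine solicited items: "abdominal pain, nausea, vomiting, diarrhoea, anorexia, fever, headache, dizziness and allergic reaction". They are first asked about after the dose: "All schoolchildren enrolled in the study will be administered with a questionnaire 4 hours after treatment for the following signs and symptoms". On day 1 the children are "interviewed using the same questionnaire to determine whether they experienced any adverse events", and for the last safety visit "The questionnaire will be repeated on day 21-post treatment". Each item is graded by Appendix 3 and given a causality rating by Appendix 4. Section 8.3 then states the comparison: "The frequency and severity of AEs will be compared between the 2 treatment regimens".

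Two things happen on D0 before the dose (section 3.2, D0).

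- **A history questionnaire for eligibility.** "Clinical history of each schoolchild fulfilling screening criteria using questionnaire will be taken to see if the subject has acute or chronic severe disease". It also covers past reactions to praziquantel ("the questionnaire will seek to establish a history of adverse reactions associated with PZQ"), recent praziquantel and other current medication. It does not list the nine solicited items.
- **A physician's examination, with the malaria check of section 6.1.1.** A child with fever and/or "showing one or more of the following signs and symptoms, i.e., body malaise, headache, vomiting or diarrhoea will be considered to have clinical malaria" is excluded and referred.

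Table 1 marks adverse events under Day 0, but the D0 text places that assessment in the four hours after treatment.

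**The concern.** Secondary endpoint b) compares the frequency and severity of adverse events between the two doses. The other secondary endpoints rest on a baseline: egg reduction uses the screening count, and haemoglobin and weight are taken relative to their D0 values. The symptom endpoint has no such reference, and nothing in section 8 limits an adverse event to a symptom that is new or worse after the dose.

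The children are selected for intestinal schistosomiasis at 100 eggs per gram or more. Some may have abdominal pain, nausea or poor appetite on the morning of treatment. Such a child can report the symptom at 4 hours and be graded. Poor appetite would enter at Grade 2, because anorexia has no Grade 1 in Appendix 3. The same background is then added to both arms, which hides part of any true dose effect on tolerability. A later analysis plan could define adverse events differently, but it could not recover a baseline that was never collected.

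**Working it through.** **1. Which of the nine items are exposed.**

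| Solicited item (8.2) | Handled before dosing on D0? |
|---|---|
| Fever, headache, vomiting, diarrhoea | Yes: section 6.1.1 excludes the child. The fever cut-off there (37 °C) is below the lowest graded fever in Appendix 3 (37.7 °C) |
| Abdominal pain, nausea, anorexia, dizziness | No structured, graded record planned |
| Allergic reaction (Grade 1 is pruritus without rash) | No structured, graded record planned |

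Four items should therefore have a pre-dose prevalence near zero, and five remain exposed.

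**2. The protocol's own figure.** There is none for the safety comparison. The 118 per arm comes from the cure-rate calculation in section 10.2 (60% v 80%, 80% power, 5% level). The two-sided formula gives 82 per arm without continuity correction and 91 with it, as stated. Then 91 × 1.3 = 118.3, taken as 118. I use 118 as the number dosed per arm.

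**3. Model.** Let b be the share with the symptom before dosing, equal in both arms and independent of the drug effect. Let p be the probability that the drug causes the symptom in the others.

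Observed frequency = b + (1-b)p

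Observed difference = (1-b)(p60 - p40)

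Example with b = 20%, p40 = 20%, p60 = 35%:
- 40 mg/kg: 0.20 + 0.80 × 0.20 = 0.36
- 60 mg/kg: 0.20 + 0.80 × 0.35 = 0.48
- difference: 0.12 = 0.80 × 0.15

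**4. Power.** I used exact binomial enumeration of the two-sided Pearson chi-square test at 5%. The column as written uses 118 per arm and the observed frequencies. The last column uses 118(1-b) children per arm, rounded, who are symptom-free at D0, and so pays for the smaller denominator. All rates are assumptions; the protocol states none.

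| b | Observed, 40 v 60 mg/kg | Difference (points) | Power as written | Power, symptom-free at D0 |
|---|---|---|---|---|
| 0 | 20.0% v 35.0% | 15.0 | 74% | 74% |
| 2% | 21.6% v 36.3% | 14.7 | 71% | 73% |
| 5% | 24.0% v 38.3% | 14.3 | 66% | 72% |
| 10% | 28.0% v 41.5% | 13.5 | 59% | 69% |
| 20% | 36.0% v 48.0% | 12.0 | 48% | 64% |
| 30% | 44.0% v 54.5% | 10.5 | 35% | 59% |
| 40% | 52.0% v 61.0% | 9.0 | 30% | 53% |

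For an assumed 30% v 50%, power as written against symptom-free is 85% v 87% at b = 5%, 80% v 85% at b = 10% and 49% v 69% at b = 40%.

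**5. Limit of the calculation.** The last column covers only children free of the symptom at D0. A rule that counts new or worsened symptoms would also include worsening in the others. The column is therefore a guide to the gain from such a rule, not a calculation of it.

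**The case against.** Several points on the other side stand.

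- **The malaria exclusion does much of the work.** A reader might infer that all nine items are contaminated. Sections 3.2 (D0) and 6.1.1 do not support that: four are screened out before the dose.
- **Adverse-event symptoms are not the only safety measure.** Section 8.2 also uses day 21 haemoglobin to look for harm, and haemoglobin has a D0 value. Serious adverse events are handled separately.
- **The causality rating can help.** A reader might infer that it is powerless here. But the categories for unrelated and unlikely events both refer to the patient's clinical state, and the team that examines the child before dosing also assesses adverse events afterwards. An assessor may remember or have noted a complaint. What is missing is a structured, graded baseline to rely on. Section 8.3 also does not confine the comparison to related events.
- **Randomisation balances the background.** Under no true dose effect it does not favour either arm.
- **Counting rules may be left to the analysis plan.** That is fair for the definition of a countable event, but not for collecting the baseline, which has to happen before the dose.
- **The loss may be small.** At b = 2% it is two points of power (71% v 73%), and the protocol sets no power target for this endpoint.

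**Conclusion.** The point holds as a cheap improvement limited to abdominal pain, nausea, anorexia, dizziness and allergic reaction. For these items, symptoms present before dosing can be counted as adverse events in both arms. That inflates the stated frequency and multiplies the risk difference by (1-b). The expected effect is loss of precision and a pull towards no difference.

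The size cannot be fixed from the protocol. Under the assumed 20% v 35%, the gap between power as written and power in symptom-free children runs from 2 points (b = 2%) to about 23 points (b = 40%). It also assumes equal b in the arms, independence from the drug effect, and no correction through causality ratings.

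A reader might go further and infer that the trial will wrongly declare 60 mg/kg as well tolerated as 40 mg/kg. The protocol does not support that. It sets no non-inferiority or equal-tolerability rule, and neither the pre-dose prevalence nor the drug-caused rates are known.

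**What to change.** - Have the physician who already examines each child on D0 give the same nine-item questionnaire just before dosing, graded by Appendix 3.
- Add this pre-dose entry to Day 0 in Table 1, separate from the 4-hour assessment.
- In sections 8.1 to 8.3, compare between arms the symptoms that are new or of a higher grade than at D0, and state the denominator. Report the crude frequencies as well.

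The cost is a few minutes and one case report form page per child, at a visit already held with a physician, plus an amendment to Table 1 and section 8. No visit, staff member, dose or clinical rule changes. The downside is that baseline-adjusted frequencies will be lower than, and less comparable with, those of studies that did not subtract baseline; reporting the crude frequencies alongside eases this.
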